## Abstract

**Background:**

Caregivers of patients with advanced cancer shoulder immense responsibilities as they care for patients, including symptom and medication management, providing emotional support, and navigating healthcare treatment and decision-making. Due to the heavy toll of these responsibilities, caregivers are at high risk for profound mental health challenges, including anxiety, depression, and posttraumatic stress disorder. A key driver of this heightened risk for psychopathology in caregivers is existential distress, manifesting as a loss of meaning and purpose, decreased spiritual well-being, and hopelessness. Historically, psychosocial interventions targeting distress in cancer caregivers have neglected to address existential distress. Meaning-Centered Psychotherapy for Cancer Caregivers, a seven-session structured intervention, was developed to address this gap. In a pilot randomized controlled trial, the approach led to enhancements in personal meaning, benefit finding, and spiritual well-being. Here, we present a large, multi-site trial that aims to definitively examine the efficacy of Meaning-Centered Psychotherapy for Cancer Caregivers in an adequately powered study.

**Method:**

This randomized controlled trial will evaluate the efficacy of Meaning-Centered Psychotherapy for Cancer Caregivers versus Supportive Psychotherapy for Cancer Caregivers on primary (personal meaning and spiritual well-being) and secondary (anxiety, depression, sense of meaning in caregiving, benefit finding, caregiver burden, social support) outcomes at baseline, posttreatment, and at 6- and 12- months follow-up. It will also evaluate the role of sense of meaning in life as a mediator of secondary outcomes, as well as the impact of Meaning-Centered Psychotherapy for Cancer Caregivers on pre- and post-loss bereavement outcomes. Caregivers (*N* = 200) of patients with advanced (stage III/IV) solid tumor cancers from Memorial Sloan Kettering Cancer Center, Sylvester Comprehensive Cancer Center, and the community will be enrolled.

**Discussion:**

Meaning-Centered Psychotherapy for Cancer Caregivers has the potential to help alleviate existential suffering in caregivers as they manage the multifaceted demands of caring for patients with advanced cancer. This trial seeks to evaluate the efficacy of this intervention in a more robust and representative trial of cancer caregivers and extends prior research to explore mediators of improvement and the impact of the intervention on pre- and post-loss bereavement outcomes.

**Trial registration:**

ClinicalTrials.gov NCT06307535. Registered on 03/05/2024.

## Administrative information

Note: The numbers in curly brackets in this protocol refer to SPIRIT checklist item numbers. The order of the items has been modified to group similar items (see http://www.equator-network.org/reporting-guidelines/spirit-2013-statement-defining-standard-protocol-items-for-clinical-trials/).

## Introduction

### Background and rationale {6a}

Over 63 million individuals in the United States are caregivers, with a significant portion providing care to patients with life-limiting cancers [1]. Caregivers of patients with cancer take on tremendous responsibilities across the illness trajectory, assisting with symptom management [2], providing emotional support [3, 4], and navigating the healthcare team and treatment [5], all while managing other personal, family, occupational, and financial responsibilities. The burden of cancer caregiving can lead to increased levels of anxiety, depression [6], and posttraumatic stress [7]. Without timely intervention, such distress has the potential to negatively impact the care provided to patients [8–10] and can contribute to poor adjustment and psychosocial outcomes in bereavement [11, 12], such as prolonged grief disorder [13].

A key driver of these mental health outcomes is existential distress, characterized as a loss of meaning and purpose in life, decreased spiritual well-being, and hopelessness [14, 15]. Existential distress is common among caregivers due to the competing demands of caregiving and personal life goals and balancing hope for the present with an awareness of potential patient death in the future. Witnessing prolonged or aggressive medical treatment, patient suffering, or a decline in patient functioning can also contribute to existential distress [16–18]. Importantly, caregivers who experience existential distress are less likely to engage in advance care planning discussions with patients and healthcare professionals, which ultimately negatively impacts the care patients receive at the end of life [19]. As such, addressing existential distress in cancer caregivers has profound benefits for caregivers, as well as the patients for whom they provide care. When existential distress is mitigated, caregivers are better able to cultivate deeper connections with patients and strengthen their sense of meaning in caregiving. This in turn can reduce regret and unfinished business and prevent poor bereavement outcomes [20–22]. Despite these facts, existential distress has historically remained unaddressed in psychosocial interventions for cancer caregivers.

Meaning-Centered Psychotherapy (MCP) [23, 24] is an empirically supported intervention originally developed to help patients with advanced, life-limiting cancers connect to meaning and purpose, despite the challenges they face. Our team adapted MCP to assist cancer caregivers to connect to meaning and purpose and mitigate existential distress (Meaning-Centered Psychotherapy for Cancer Caregivers—MCP-C) [25, 26]. Developed with feedback from caregiver stakeholders, MCP-C is an existentially oriented seven-session manualized intervention that helps caregivers connect—or reconnect—to sources of meaning and purpose in their life despite the challenges, limitations, and losses that come with caregiving. Our pilot trial of MCP-C among 60 caregivers of patients with glioblastoma evidenced strong preliminary effects on enhanced personal meaning, benefit finding, and spiritual well-being. The results of this pilot randomized controlled trial, alongside qualitative feedback from participants that supported its feasibility and acceptability [27], suggested that MCP-C should be tested in a larger, fully powered randomized controlled trial.

## Objectives {7}

This randomized controlled trial has three objectives. The primary objective of this study is to investigate the efficacy of MCP-C versus Supportive Psychotherapy for Cancer Caregivers (SP-C) on primary (i.e., sense of meaning in life, spiritual well-being) and secondary (i.e., anxiety, depression, sense of meaning in caregiving, benefit finding, caregiver burden, social support) outcomes immediately posttreatment and explore maintenance in improvements up to 1-year posttreatment (Aim 1). The secondary objectives of this study are to evaluate the role of sense of meaning in life as a mediator of improvements in key secondary outcomes (Aim 2) and explore the effects of MCP-C on pre- and post-loss grief and bereavement outcomes (Aim 3).

## Trial design {8}

This is a randomized controlled trial in which participating caregivers (*N* = 200) are randomized 1:1 in a parallel group design to either MCP-C or SP-C to test the efficacy (superiority) of MCP-C versus SP-C.

## Methods: participants, interventions, and outcomes

### Study setting {9}

The coordinating site for this trial is the Icahn School of Medicine at Mount Sinai (ISMMS). Participants are being recruited from two primary sites: Memorial Sloan Kettering Cancer Center (MSK) and Sylvester Comprehensive Cancer Center (SCCC), part of the University of Miami Health System. Caregivers will also be recruited through the community via the National Alliance for Caregiving and the American Cancer Society, who will share information about this trial with their listservs and on their social media platforms. Information about study participation will be included on all advertisements and posts, and caregivers will be directed to contact ISMMS to learn more about study participation.

### Eligibility criteria {10}

Participants are eligible if they are as follows: At least 18 years of age, can read and understand English, a self-reported current caregiver to a patient with Stages III or IV solid tumor cancer currently receiving any type of medical treatment (e.g., curative, palliative), reporting caregiving-related distress as evidenced by scoring a 4 or greater on an adapted distress thermometer (DT) for caregivers, residing in New York, New Jersey, Florida, or Connecticut, or have the ability to complete sessions in compliance with current telehealth regulations. Participants are not eligible if they do not have a reasonable understanding of study procedures as judged by the consenting professional or if they are engaged in regular individual psychotherapeutic support that they are unable or unwilling to pause while receiving the study intervention.

MCP-C and SP-C interventionists will be eligible if they have, at minimum, a master’s degree and at least 1 year of prior clinical experience. They will be drawn from the disciplines of psychology, psychiatry, and social work with appropriate training and knowledge of individual therapeutic dynamics.

### Who will take informed consent? {26a}

Study team members trained in informed consent procedures will screen eligible participants, explain study procedures, and enroll caregivers who meet study inclusion criteria and provide informed consent. These consent conversations will occur over the telephone, and participants will self-report if they are able to comply with telehealth regulations throughout the MCP-C/SP-C sessions, that is, be physically located in states where interventionists are licensed during sessions.

### Additional consent provisions for collection and use of participant data and biological specimens {26b}

No ancillary studies or biological specimen collection is planned.

## Interventions

### Explanation for the choice of comparators {6b}

We are comparing MCP-C, the study intervention, to SP-C. SP-C is based on a model of supportive psychotherapy that has been used in previous randomized trials of MCP as the comparator intervention and was adapted to represent the standard of caregiver support in the community. It has also been standardized for use in RCTs [28].

### Intervention description {11a}

#### Meaning-Centered Psychotherapy for Cancer Caregivers (MCP-C)

MCP-C is a seven-session intervention delivered individually over telehealth platforms that combines didactics, discussion, and experiential exercises focused on themes related to meaning and caregiving. Each session is an hour long. Session 1 (*Concepts and Sources of Meaning*) provides an overview of meaning and caregiving and asks participants to share their caregiving journey and their understanding of the word “caregiver.” Session 2 (*Identity Before and After Becoming a Caregiver*) focuses on how caregiving impacts participants’ identities, highlighting both immutable aspects as well as the possibility for growth. Session 3 (*Historical Sources of Meaning*) focuses on the meaning derived through reflecting on one’s past legacy (i.e., family history and past life experiences that one does not choose), the present legacy caregivers are actively creating, and the future legacy they will give to others. Session 4 (*Attitudinal Sources of Meaning*) focuses on helping caregivers to recognize where they have choice and how meaning can be derived through reflecting on how they choose to respond to life’s limitations and challenges, including how they choose to face the potential eventual death of their care partner. Session 5 (*Creative Sources of Meaning*) focuses on meaning generated through creating one’s life (i.e., the activities they do or pursuits or interests that make them who they are) and highlights self-care as a key route through which caregivers can continue to create their lives, despite the challenges of caregiving. Session 6 (*Experiential Sources of Meaning*) focuses on meaning derived through experiencing life through the five senses and through the experiences of love, beauty, and humor. Session 7 (*Transitions*) reviews the material covered and provides space to reflect on the ways participants can continue to use these sources of meaning as resources moving forward. At the end of each session, caregivers are encouraged to reflect on questions specific to the subsequent session’s theme for homework to help guide discussion and reflection.

#### Supportive Psychotherapy for Cancer Caregivers (SP-C)

SP-C is a seven-session intervention delivered individually over telehealth platforms based on conceptual models developed by Rogers [29] and Block [30]. Each session is an hour long. SP-C incorporates client-centered, supportive strategies and offers caregivers a safe space to share challenges they face in their daily routines and experiences. For each session, the topic of discussion is determined by the caregiver and centers on their most pressing caregiving-related need at that time. Unlike in MCP-C, the therapist does not impose a structure or agenda onto the session. The role of the therapist is to provide supportive reflections, to acknowledge and validate their emotions and reactions in response to the caregiving role, to encourage caregivers’ self-reflection, and to highlight adaptive coping responses to challenges, including support-seeking and self-care strategies. Therapists utilize curiosity, acceptance, and openness to facilitate the therapeutic alliance to assist caregivers to explore and validate their experiences. SP-C has been utilized and standardized in past RCTs of MCP and tailored for cancer caregivers.

### Criteria for discontinuing or modifying allocated interventions {11b}

Discontinuing the allocated intervention will only occur if the participant chooses to end their participation in the study or is no longer able to comply with telehealth regulations. Participants will not be able to modify their allocated intervention arm once randomized. There are no significant concerns of harm from either study arm that would require a change in study arm allocation. If participants become bereaved, they are welcome—and encouraged—to remain on the study, and bereavement-related adaptations are made to subsequent sessions.

### Strategies to improve adherence to interventions {11c}

We encourage participants to complete study sessions weekly and will be flexible with their schedule if they need to reschedule a session for a later date. We expect that the seven study sessions will be completed within 14 weeks. This schedule flexibility will help to improve adherence to the intervention. All intervention sessions are audio/video recorded, and a random sample of 30% of cases (100% of sessions for these participants) will be evaluated and rated for treatment integrity by independent raters throughout the study. We have developed comprehensive treatment manuals for MCP-C and SP-C to facilitate standardized delivery, and all interventionists undergo a half-day training in either MCP-C or SP-C, followed by weekly group supervision sessions. Supervisors also review recorded sessions to facilitate reinforcement of model-specific strategies and alert therapists of any drift in model adherence. To reduce likelihood of treatment contamination, each condition is delivered by distinct treatment providers. Further, therapists monitor attendance and homework completion when relevant as part of session notes. Deviations from the protocol are recorded and discussed regularly during weekly group supervision.

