### Participant timeline {13}

Potential participants will be screened for eligibility (approximately 5 min) and will meet criteria if they report distress ≥ 4 on the distress thermometer and indicate that the distress is related to caregiving. If interested, participants will complete informed consent procedures and will be offered to immediately complete baseline (T1) assessments. Participants will have up to 45 days (consent expiration) to complete baseline assessments. Once baseline assessments are complete, they will be randomized to either MCP-C or SP-C and assigned to a therapist for seven individual sessions that will be completed over Webex. Participants will have up to 14 weeks to complete all seven sessions. After intervention completion, participants will complete follow-up assessments immediately posttreatment (T2, +2 weeks), 6-month follow-up (T3, ±4 weeks), and 12-month follow-up (T4, ±8 weeks). See Fig. 1 for the full study timeline.

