### Sample size {14}

Participants will be 200 caregivers recruited across study sites and the community, with 100 caregivers randomized to each study arm (MCP-C vs. SP-C). The sample size was chosen to provide 80% power to detect reasonable treatment effect sizes for our two primary endpoints while maintaining the type 1 error rate at *α*= 0.05 for these comparisons. Using methods relevant to clinical trials with repeated measures [31], we calculated the smallest effect size that we will be able to detect for the immediate posttreatment coefficient of the time-by-arm interaction term in our linear mixed model analysis of one of the two primary outcome measures (LAP-R PMI). Given the sample size (*N* = 200), we will be able to detect a standardized mean difference treatment effect size between the two study arms of 0.48 standard deviations. This calculation assumed a correlation between baseline and follow-up measures of 0.5, 20% attrition by the posttreatment assessment, a two-sided significance test, and a type 1 error of 0.025 (0.05 overall for both primary endpoints).

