#### Aim 1: Analytic plan

The primary and secondary outcome measures for Aim 1 are all continuous variables assessed repeatedly over the four time points: baseline (T1), immediately posttreatment (T2), 6-month follow-up (T3), and 12-month follow-up (T4). The co-primary efficacy endpoints for Aim 1 are the LAP-R PMI and FACIT SWBS at the immediately posttreatment assessment (T2). We will consider MCP-C efficacious if MCP-C participants have significantly greater improvements than SP-C participants in LAP-R PMI or FACIT SWBS scores at T2 at the *p*< 0.025 statistical significance threshold in the analysis described below. We will analyze each continuous primary and secondary outcome measure by using constrained linear mixed model (cLMM) regression [52–54]. This statistical method accounts for within-subject correlations due to repeated measurement of participants and, under the reasonable missing at random (MAR) assumption, allows unbiased estimation of between-group differences without excluding participants with missing follow-up data. Each of these outcome measures will be analyzed using a separate cLMM regression with random intercept that will model the baseline and repeated follow-up scores (dependent variable) as a function of time (categorical) and the time-by-arm interaction, controlling for the randomization stratification variable (study site). The cLMM method will also constrain the two study arms to have a common baseline mean on the outcome measure to reflect the pre-randomization nature of the baseline assessment (T1) [52]. All randomized participants will have, at a minimum, the baseline (T1) primary outcome assessments and will be included in the cLMM per the intention-to-treat principle. In the cLMM parameterization, the coefficients for the time-by-arm interaction are equivalent to the differences between arms in outcome measure score changes from baseline to the post-baseline time points, and they will be calculated with 95% confidence intervals (CIs). For each co-primary endpoint (LAP-R PMI and FACIT SWBS), we will conclude that MCP-C participants had significantly larger improvements in the endpoint at T2 compared to SP-C if the time-by-arm interaction coefficient for T2 is significantly larger than 0 at the *p* < 0.025 level. The secondary outcome measures will be compared between study arms using similar cLMM analyses. However, we will assess estimated treatment effects at each timepoint using 95% CIs instead of *p*-values.

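### Therapists are nested within arm, but the primary model and the sample size have no therapist term; if therapist ICC is above zero, the per-endpoint type I error exceeds 0.025

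*Protocol article*

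**What the plan says.** Four places in the protocol article bear on this.

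- **Strategies to improve adherence {11c}**: "To reduce likelihood of treatment contamination, each condition is delivered by distinct treatment providers". No therapist delivers both treatments. On preparation, "all interventionists undergo a half-day training in either MCP-C or SP-C, followed by weekly group supervision sessions".
- **Participant timeline {13}**: once randomized, the caregiver is "assigned to a therapist for seven individual sessions that will be completed over Webex".
- **Aim 1: Analytic plan**: "Each of these outcome measures will be analyzed using a separate cLMM regression with random intercept". The fixed part is categorical time, the time-by-arm interaction and study site, with a common baseline mean. The stated purpose is repeated measurement: "This statistical method accounts for within-subject correlations due to repeated measurement of participants". The intercept is therefore read as belonging to the participant. MCP-C counts as efficacious if either co-primary endpoint reaches p < 0.025 at T2.
- **Sample size {14}**: 100 caregivers per arm, a detectable difference of 0.48 SD, 80% power, two-sided error of 0.025 per endpoint. On its assumptions: "This calculation assumed a correlation between baseline and follow-up measures of 0.5, 20% attrition by the posttreatment assessment".

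No section mentions a therapist effect, a therapist ICC, a design effect or a related sensitivity analysis. The section on additional analyses repeats only the adjustment for site.

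**The concern.** Caregivers who share a therapist may have more similar post-treatment scores than caregivers who do not. If therapists worked in both arms, much of the difference between them would cancel in the arm comparison. With separate therapists for each arm nothing cancels, and all between-therapist variance goes into the arm contrast. A participant-level intercept cannot see that variance, and adjusting for site does not remove differences among therapists within an arm.

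At stake are the p-values of both co-primary tests, the 95% confidence intervals on which the secondary outcomes will be judged, and the power claim. A positive result could partly reflect which therapists happened to deliver MCP-C.

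**Working it through.** **Inputs from the article.** 100 per arm; 20% attrition by T2, so 80 per arm; baseline to follow-up correlation 0.5; two-sided error 0.025, so z = 2.2414; 80% power, so z = 0.8416.

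**Inputs that have to be assumed.** Number of therapists per arm, k, with equal caseloads; and therapist ICC.

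**1. The plan's own figure.** The SD of a change score is √(2(1 − 0.5)) = 1. With independent caregivers the standard error is √(2/80) = 0.1581, and the detectable difference is (2.2414 + 0.8416) × 0.1581 = 0.4875 SD. Power at 0.48 SD is Φ(0.48/0.1581 − 2.2414) = 0.787. Both agree closely with the stated 0.48 SD and 80%, so on this variance the figure implies a design effect of 1. A baseline-adjusted variance (SD √0.75) gives 0.422 SD and does not match.

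**2. Simple design-effect formula.** With m = 80/k caregivers per therapist, DE = 1 + (m − 1) × ICC. The actual error of a nominal 0.025 test is 2(1 − Φ(2.2414/√DE)). For k = 5 and ICC 0.05: m = 16, DE = 1 + 15 × 0.05 = 1.75, 2.2414/1.3229 = 1.694, error 0.090.

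**3. Simulation under the null.** The stated cLMM (random intercept, common baseline mean, site, REML) was simulated 4,000 times per setting, with the therapist effect acting on post-baseline visits only. At ICC 0 the rejection rate was 0.024, as it should be. A second simulation, of a simpler baseline-adjusted analysis, gave 0.068 (k = 10) and 0.121 (k = 5) at ICC 0.05.

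| Therapists per arm | ICC | DE | Error, formula | Error, simulation |
|---|---|---|---|---|
| 20 | 0.01 | 1.03 | 0.027 | about 0.03 |
| 10 | 0.02 | 1.14 | 0.036 | about 0.04 |
| 10 | 0.05 | 1.35 | 0.054 | 0.064 to 0.068 |
| 5 | 0.05 | 1.75 | 0.090 | 0.121 to 0.128 |

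**4. Why simulation exceeds the formula.** Using the baseline reduces the residual variance but not the therapist variance, so the therapist share grows. At k = 5 and ICC 0.05 the therapists add 2 × 0.05/5 = 0.020 to the variance of the contrast. Without clustering the cLMM standard error is 0.137, and √(0.137² + 0.020) = 0.197. The simulated SD was 0.198, while the model reported a mean standard error of 0.135. Then 2(1 − Φ(2.2414 × 0.135/0.198)) is about 0.13. For k = 20 and ICC 0.01 the addition is 0.001, √(0.137² + 0.001) = 0.141, and the same calculation with a model standard error of 0.137 gives about 0.03.

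**5. Power if therapist is accounted for.** On the plan's own basis (step 1) at ICC 0.05, the detectable difference is 0.4875 × √1.35 = 0.57 SD (k = 10) or 0.4875 × √1.75 = 0.65 SD (k = 5). Power at 0.48 SD falls from 0.79 to Φ(3.036/1.162 − 2.2414) = 0.65 or Φ(3.036/1.323 − 2.2414) = 0.52. These are normal approximations; small-sample degrees of freedom would lower power somewhat further.

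**The case against.** The strongest objection is that the consequence depends on two numbers the article does not give. With an ICC of exactly zero there is no inflation. With 20 therapists per arm and ICC 0.01 the error is 0.027 to 0.03, close to nominal. Section {11c} also describes manuals, weekly supervision, review of recordings for drift and integrity rating of 30% of cases, all of which tend to make therapists more alike. This stands, and it is why the size is given only as a range. It does not remove the point: nothing in the article supports assuming an ICC of zero.

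A reader might infer more than the text supports:

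- that every therapist carries a large caseload. No caseload or therapist number is stated;
- that each arm has its own supervision group. Training is by arm, but the article does not say that the weekly group supervision is;
- that the therapist is already held as an analysable data field. Only the assignment is described;
- that the overall 0.05 is certainly breached. Splitting the error as 0.025 and 0.025 leaves slack when the endpoints are correlated. At a per-endpoint error of 0.027, two test statistics correlated at 0.6 (assumed) give an overall error of about 0.049.

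It can also be said that 0.48 SD need not imply independence, because a baseline-adjusted variance with a design effect of (0.48/0.422)² = 1.29 would give the same figure. That is arithmetically true, but the section lists its assumptions and clustering is not among them.

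Finally, this is a condensed article, and degrees-of-freedom methods or sensitivity analyses may be in the full protocol or analysis plan. That would answer a complaint about missing detail. Here the article states the primary model, and the model as stated does not fit the stated delivery of treatment.

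**Conclusion.** The point holds in conditional form. Therapists are nested in arm, each caregiver is assigned to one therapist, and the stated primary model has no term for therapist. For any therapist ICC above zero, with therapists treating more than one caregiver, the model standard error is too small and the type I error exceeds 0.025 per endpoint. The documents do not show that the ICC is positive, so they do not support saying that the error rate is certainly exceeded, or by a particular amount.

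Over the assumed settings the per-endpoint error runs from about 0.03 to about 0.13 in simulation; the simple formula understates this for the stated model (0.027 to 0.090). Whether the overall 0.05 is exceeded depends on the same inputs and on the correlation between the endpoints. Where one endpoint alone passes 0.05, as in both ICC 0.05 settings, the overall rate does so whatever the correlation. The 0.48 SD detectable effect likewise holds only without therapist clustering on the change-score basis that reproduces it.

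**What to change.** 1. Add a therapist random effect to the Aim 1 cLMMs, nested in arm and acting on post-baseline visits only, since T1 precedes therapist assignment. Use Kenward-Roger or Satterthwaite degrees of freedom.
2. Report the therapist ICC for each co-primary endpoint.
3. Restate the detectable effect in the sample size section under a stated number of therapists and an assumed ICC. At ICC 0.05 it would read about 0.57 SD with 10 therapists per arm or 0.65 SD with 5.
4. Confirm that the treating therapist is captured as a data field for every participant.

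The cost is wider confidence intervals, fewer degrees of freedom and lower stated power at 0.48 SD: about 0.65 or 0.52 instead of 0.79 in those two cases. No additional enrolment is required to make the change. Recruitment is expected to run to March 2028 and no interim analysis is planned, so the model can be amended before any comparison of outcomes by arm.
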